### Eligibility criteria

#### Inclusion criteria

Adult men and women, 18 years of age or olderResident of Karachi and planning to live in Karachi till the follow-up periodAble to understand Urdu (language of the videos)Admitted with first ever stroke (ischemic or hemorrhagic stroke)Modified Rankin score (mRS) ≤4 ( mild to moderate stroke)Have at least one vascular risk factor that requires medical interventionConsenting to participate in the study and follow-up, both stroke survivor and caregiverHave a stable surrogate caregiver at home who is responsible for appointments, follow-ups, overall care, e.g., wife, daughters, daughter- in- law, husbandStroke is medically stable and participant is likely to return to the community after the in- hospital stay (thus, actively treated strokes, e.g., decompressive surgeries, carotid endarterectomy (CEA), in-hospital sepsis, ventilator complications) that essentially preclude return to the community settings will not be offered this chronic care support study

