### Exclusion criteria

Serious aphasia, visual hemi-neglect, short-term memory loss in the stroke survivor precluding understanding, visualization or retention of the video material (will be measured through the NIH Stroke Scale performed by trained physicians; those having a score of greater than 4 due to aphasia alone will be excluded)Serious aphasia, visual hemi-neglect, short-term memory loss, dementia in the caregiver precluding understanding, visualization or retention of the video material (will be measured through the NIH Stroke Scale performed by trained physicians; those having a score of greater than 4 due to aphasia alone will be excluded, dementia status will be assessed by the Mini-Mental State Examination)Iatrogenic stroke, i.e., stroke due to non-atherosclerotic vascular disease and rare causes, e.g., carotid dissections, gunshot wounds to the neck, post coronary artery bypass grafting (CABG)Stroke survivor/Caregiver dyad continue post-stroke care in a nursing assisted, professional or hospital setting and do not return to the community after dischargeSerious concurrent medical illnesses, like cancer, renal failure, acute liver disease in past 6 months (that precludes the use of statins), chronic liver disease that excludes the use of stroke preventive medications, or require non-standardized therapyUse of any off-label, non-guideline medications which, due to stroke survivors’ unique co-morbidities, interfere with medication compliance to antihypertensives, statins, antiplatelet agents and diabetes control

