### Identification and enrollment of the study participants

Data collectors will screen the participants coming to AKUH Stroke Unit, Neurology ward, Karachi. Data collectors will fill out the eligibility form and, if the participants are found eligible for the study, they will be officially invited to participate in the trial. Informed consent will be obtained from those participants who voluntarily wish to be in our study. The study participants and their caregivers will be thoroughly counseled about the nature of the study and required follow-up. It will also be explained to study participants that the selection in the study group is random. Stroke survivors will then undergo a detailed interview regarding the socio-demographic, clinical and functional assessment at baseline. Then, the participants will undergo randomization to either the intervention group or standard care group. After allocation assignment, the research supervisor will thoroughly explain the details of the software program and its installation and then proceed with the delivery of the first set of 5- minute videos. Any questions pertaining to the use and the comprehension of the videos and software will be answered. Videos will be shown at the time of enrollment into the study, at discharge from the hospital, and follow-up at first and third months post discharge and a memory card containing the Stroke4Movie Application will be installed and programmed to deliver scheduled videos on the participant’s Android phone. In case of the participant being allocated to the usual care group they will be informed about the details regarding discharge and the follow-up appointments at the clinic (Refer to Fig. 2) (see Additional files 1, 2 and 3).

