### Secondary end-points

To analyze the secondary outcome, caregivers’ mean score of knowledge regarding stroke risk factors, stroke rehabilitation and medications at each follow-up visit between the two groups will be calculated through Student’s *T* test if the outcome is symmetrically distributed or the Mann-Whitney *U* test if the outcome is not symmetrically distributed.

The proportion of participants with respect to readmission to hospital with any of the stroke-related complications between the two groups will be calculated either by Pearson’s chi-square test or Fischer’s exact test (if the expected cell count is less than 5).

The proportion of participants with respect to stroke-related mortality between the two groups will be calculated either by Pearson’s chi-square test or Fischer’s exact test (if the expected cell count is less than 5).

The change in mean score of National Institutes of Health Stroke Scale (NIHSS), Barthel Index and mRS from baseline at each follow-up visit between the two groups, will be calculated through Student’s *T* test if the outcome is symmetrically distributed or the Mann-Whitney *U* test if the outcome is not symmetrically distributed.

The change in mean scores for level of satisfaction with the intervention and acceptability of mHealth innovation at the third month follow-up visit post discharge between the two groups will be calculated through Student’s *T* test if the outcome is symmetrically distributed or the Mann-Whitney *U* test if the outcome is not symmetrically distributed.

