### Secondary study outcomes

Change in knowledge of caregivers concerning stroke risk factors, stroke rehabilitation and medications (a knowledge questionnaire will be administered at 1, 3, 6, 9 and 12 months post discharge and change in score will be ascertained)Readmission to hospital with any of the stroke-related complications – urinary tract infection, pneumonia, and deep venous thrombosis (this information will be elicited at the follow-up time, based on recall. All participants will be asked to bring documents related to any hospital admissions in the period following discharge)Stroke-related mortality will be assessed through a Verbal Autopsy Scale adopted from the WHO [15]Change in functional outcome (severity and disability after stroke) from baseline among stroke survivors will be assessed through validated tools (NIHSS, Barthel Index and mRS) [16]Level of satisfaction with the intervention and acceptability of mHealth innovation such as videos on selected topics among stroke survivors and caregiver dyads to improve clinical outcomes. This will be done on a self-designed tool which ascertains the constructive and unpleasant attributes of using this mHealth technology (please refer to Form C, Data Collection Form for Stroke Survivors– see Additional file 1). This self-designed tool will be administered by a research supervisor who will be unblinded to the randomization group. This tool has design attributes based on Rogers’ Diffusion of Innovation Theory for ease, adoption, repeatability, and adaptability [17].

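### Readmission and stroke-related mortality get only unadjusted tests, with no between-arm estimate and interval, although baseline severity is available before randomisation: valid, but some precision is forgone

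*Protocol article*

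**What the plan says.** The article's section Secondary end-points fixes one analysis for each event outcome. For readmission with a stroke-related complication: "The proportion of participants with respect to readmission to hospital with any of the stroke-related complications between the two groups will be calculated either". The two options named there are Pearson's chi-square and, with small expected counts, Fisher's exact test. For deaths: "The proportion of participants with respect to stroke-related mortality between the two groups will be calculated either by Pearson’s chi-square test". Fisher's exact test is again the alternative. Neither sentence names a covariate, an effect measure or an interval. The regression described under Univariate analysis and Multivariable analysis is tied to the primary end-point, so it does not reach these two outcomes.

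Severity is measured early. Under Identification and enrollment of the study participants: "Stroke survivors will then undergo a detailed interview regarding the socio-demographic, clinical and functional assessment at baseline". The next sentence reads: "Then, the participants will undergo randomization to either the intervention group or standard care group". Eligibility needs "Modified Rankin score (mRS) ≤4", and the aphasia and neglect exclusions "will be measured through the NIH Stroke Scale performed by trained physicians". Under Secondary study outcomes, change in functional outcome "from baseline among stroke survivors will be assessed through validated tools (NIHSS, Barthel Index and mRS", so baseline values of all three scales must exist.

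The sections Randomization process and Allocation concealment mention a random number list and a block size, but no stratification by severity.

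**The concern.** Death and complication readmission are infrequent outcomes, so each comparison rests on limited information. If initial severity predicts these events, a test that ignores it leaves explainable variation in the error term, and the comparison is less precise than the collected data allow. The plan also stops at a test. Without a prespecified risk difference and interval, a reader of a non-significant result cannot see which differences the trial has ruled out. At stake is modest precision on two secondary outcomes and a clear estimate for each; the validity of the trial is not in question.

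**Working it through.** **Is there a figure to reproduce?** No. The article gives no power or precision for readmission or mortality. Its stated 95 % power concerns the primary end-points and does not bear on this point.

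**Inputs from the article.** 150 per arm (Sample size calculation). First-year mortality after discharge of 12 % in a hospital-based Pakistani study (Background), used only as an illustrative risk.

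**Assumptions.** One severity score x, standardised to mean 0 and SD 1. Odds ratio per SD of 1.5, 2 or 3. Event risk of 5, 12, 20 or 30 %. No treatment effect. Two-sided 5 % level.

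**Formula.** Let p(x) be the logistic risk at severity x, with mean p.
- Crude variance of the risk difference: 2p(1−p)/n.
- Adjusted variance, approximately: 2E[p(x)(1−p(x))]/n.
- Since E[p(x)(1−p(x))] = p(1−p) − Var(p(x)), the relative reduction is Var(p(x)) / [p(1−p)].

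Example, p = 0.12 and odds ratio 3: Var(p(x)) = 0.0128 and p(1−p) = 0.1056, so the reduction is 0.0128/0.1056 = 12 %.

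The table gives the reduction from the formula, then from 20,000 simulated trials of 150 per arm (crude against standardised risk difference; Monte Carlo error at most 0.6 points).

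| Event risk | Expected events in 300 | Odds ratio 1.5 | Odds ratio 2 | Odds ratio 3 |
|---|---|---|---|---|
| 5 % | 15 | 0.8 / 0.5 % | 2.6 / 2.1 % | 7.1 / 6.6 % |
| 12 % | 36 | 1.8 / 1.4 % | 5.1 / 4.8 % | 12.2 / 11.4 % |
| 20 % | 60 | 2.6 / 2.7 % | 7.1 / 6.6 % | 15.6 / 15.3 % |
| 30 % | 90 | 3.3 / 2.4 % | 8.7 / 8.7 % | 18.1 / 17.5 % |

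Runs of 2,000 trials gave similar ranges (about 0 to 5 % at 5 % risk, about 2 to 11 % at 12 %, up to about 16 % at 20 to 30 %). Their Monte Carlo error is 1 to 2 points at the strongest setting.

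**What this means for the interval.** At 12 % risk the crude 95 % half-width is 1.96 × √(2 × 0.1056/150) = 7.35 points. With the largest simulated reduction at that risk it becomes 7.35 × √(1 − 0.114) = 6.9 points.

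**Power, as an indication.** These are 2,000 simulated trials with 12 % against 5 % and 150 per arm, comparing the crude chi-square test with an adjusted likelihood-ratio test. Power went from 0.587 to 0.611, from 0.599 to 0.651 and from 0.594 to 0.660 for log-odds of 0.5, 0.8 and 1.2 per SD (odds ratios of about 1.6, 2.2 and 3.3). Part of the gain may come from the different test statistic.

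**Error rate.** With no difference between arms, at 12 % and 65 % risk, the crude test rejected in 4.5 to 5.0 % of trials and the adjusted test in 4.5 to 5.4 %. Mean crude and adjusted risk differences agreed within 0.001.

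**Chance imbalance.** An imbalance in severity of 1.96 standard errors is 1.96 × √(2/150) = 0.226 SD. Its effect on the risk difference is approximately 0.226 × ln(odds ratio) × p(1−p). At 12 % risk and odds ratio 2 this is 0.226 × 0.693 × 0.1056 = 1.65 points (1.57 by exact integration). For odds ratios 2 to 3 the exact shift is 1.6 to 2.3 points at 12 % risk and 2.3 to 3.4 points at 20 %. The crude half-widths are 7.35 and 9.05 points, so the shift is about 0.2 to 0.4 of a half-width.

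**The case against.** A chi-square or Fisher test on randomised arms is a standard, sound analysis of a secondary event proportion. A supportive adjusted model could also sit in a full analysis plan that is not shown. Both statements are fair. The article does, however, name its tests under its own heading for the statistical analysis, and as written these are the only analyses given for the two outcomes.

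The event risks may be generous. The 12 % is first-year mortality in another hospital-based group, whereas this trial counts stroke-related deaths in medically stable patients with mRS up to 4. Readmission is limited to three named complications, and the article gives no rate for it. At 5 % risk the gain is small and about 15 events would support little modelling. This stands, and it is why the fix uses one covariate and a fallback.

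The prognostic strength is assumed, and the mRS limit narrows the severity range. This also stands. That NIHSS is recorded at the pre-randomisation baseline is inferred from the passages above, because the data forms are in additional files not shown.

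A reader might infer that the crude comparisons are biased, or that an unlucky severity imbalance could pass for benefit or harm of the videos. The documents do not support this. Over randomisation the crude estimate is unbiased, and its standard error already includes chance imbalance; even a roughly 1-in-20 imbalance moves the result by well under half of the crude half-width.

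A reader might also infer that no effect size will be seen. That goes too far: the article commits to frequencies and percentages for categorical data, so the crude difference can be read off. What is unspecified is a between-arm estimate with an interval.

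**Conclusion.** The point holds as a minor, nearly free improvement. The planned tests are valid, but they leave collected prognostic information unused and stop short of an estimate with an interval. With 150 per arm and odds ratios of 1.5 to 3 per SD of severity, adjustment would reduce the variance of the risk difference by about 1 to 11 % at 12 % risk, by up to about 15 to 17 % at 20 to 30 %, and by about 0 to 7 % at 5 %. With a weak predictor the gain is at most about 3 % at any of these risks. The direction is firm. The size rests on a prognostic strength and event risks that the documents do not supply. The absence of stated stratification explains why severity may differ by chance, but it is not itself an error.

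**What to change.** For readmission and for stroke-related mortality, prespecify the risk difference with a 95 % interval, standardised over all analysed participants from a logistic model with arm and one baseline severity score, continuous NIHSS. Report the risk difference and not the model's odds ratio: the precision gain does not appear as a smaller standard error of a conditional odds ratio. Keep the chi-square or Fisher test as the unadjusted check.

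State in advance, on the pooled event count, when the unadjusted analysis or a penalised fit takes over; fewer than about 20 events would be a workable threshold. At 5 % risk (about 15 events) the fallback would usually apply, and little is lost because the gain there is small.

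The cost is analysis wording, provided that the baseline form holds NIHSS as the text implies. The one downside is a model that may be unstable with sparse events, which the fallback covers.

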## Background

The World Health Organization (WHO) defines stroke as “a focal (or at times global) neurological impairment of sudden onset, and lasting more than 24 hours (or leading to death) and of presumed vascular origin” [1]. Two thirds, i.e., 36 million of the estimated 56 million deaths worldwide are attributed to non-communicable diseases (NCD), primarily stroke. Over 80 % of strokes now occur in LMICs [2], with 15 million strokes occurring annually worldwide, leaving five million dead, and five million permanently disabled. One person suffers a stroke every 45 seconds; one person dies of a stroke every 4 minutes [3]. Globally, stroke accounts for 46.6 million disability adjusted life-years (DALYs) [4].

NCD and stroke are becoming an important issue in Pakistan as the country undergoes demographic transition [5]. Pakistan, the sixth most populous nation in the world, has a distinctively stroke-prone population. Today, about one in four adult Pakistanis has hypertension and/or diabetes, heart disease, or a stroke equivalent [6]. Yet, early detection and risk reduction would have prevented stroke in 80–90 % of victims [7]. A local study conducted on one ethnicity (Pashtoon), reported a prevalence of 4.8 %, which would translate into four million persons in a country of 180 million [6]. In another hospital-based study, 65 % of adult Pakistani stroke survivors reported at least one post-stroke complication and a 12 % mortality in the first year post discharge [8].

This high-risk population is also highly underserved. Health systems are acutely responsive and are not equipped to respond to chronic diseases. There is not a single inpatient comprehensive rehabilitation system. Since the recent democratic reforms and 18th Constitutional Amendment, an opportunity has arisen for health reform, where devolution has resulted in provincial autonomy for health [9]. Thus, evidence for a systematized, replicable, scalable and effective response to chronic disorders is much more likely to be adapted.

In 80 % of stroke victims, further events may be prevented by altering lifestyle risk factors, and increasing adherence to medications to control hypertension, diabetes and hyperlipidemia [10–12]. However, there exists an implementation gap to adopt widely recognized beneficial medicines and lifestyle changes after stroke [6].

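### NIHSS, Barthel Index and mRS are compared by unadjusted change from baseline, although a pre-randomisation baseline is collected and adjusting for it would be at least as precise

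*Protocol article*

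**What the plan says.** Under Secondary end-points, the quantity compared between arms is "The change in mean score of National Institutes of Health Stroke Scale (NIHSS), Barthel Index and mRS from baseline at each follow-up visit". The test is Student's t, or Mann-Whitney U if the outcome is not symmetric. No covariate is named. Under Secondary study outcomes, change in functional outcome "from baseline among stroke survivors will be assessed through validated tools (NIHSS, Barthel Index and mRS") is listed without further analysis detail.

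The baseline exists before allocation. Under Identification and enrollment of the study participants: "Stroke survivors will then undergo a detailed interview regarding the socio-demographic, clinical and functional assessment at baseline". Randomisation comes after that step. Entry requires "Modified Rankin score (mRS) ≤4".

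The regression described under Univariate analysis and Multivariable analysis is built on the primary end-point, so it does not supply an adjusted analysis of the functional scales.

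Stroke-related deaths have their own test: "The proportion of participants with respect to stroke-related mortality between the two groups will be calculated either by" chi-square or an exact test. The article gives no rule for how a patient who has died enters the NIHSS, Barthel or mRS comparison, and it does not restrict that comparison to patients alive at the visit.

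**The concern.** Subtracting baseline amounts to fixing its regression coefficient at 1. If the true slope of follow-up on baseline is lower, the subtraction adds noise. That is plausible here. The Study design section places randomisation within 48 hours of stroke, a period when function can change quickly (although the Stroke survivor definition allows up to 6 weeks). Because the article names the test, this is a stated choice and not a detail left open. An adjusted analysis would have to replace that choice.

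What is at stake is precision on the disability outcomes. The article says promising results would lead to a larger trial on mortality and disability, so these comparisons are likely to inform that decision.

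The silence on deaths is a lesser matter. If deaths differed by arm, the functional result would depend on how they were counted.

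**Working it through.** **Plan's own figure.** There is none for these scales. The 300 dyads and the power of at least 95 % under Sample size calculation belong to the primary end-points. They are used below only to get an evaluable number.

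**Inputs.**
- 150 per arm with 10 % attrition (Sample size calculation): 150 × 0.9 = 135 per arm, 270 in total.
- r, the correlation of baseline with follow-up on the same scale: not in the document. Assumed 0.3 to 0.9.
- Two-sided 5 % level: assumed.
- s0 and s1, the standard deviations at baseline and follow-up: not in the document. First taken as equal (s).

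**Variances per patient, equal SDs.**
- Follow-up score alone: s².
- Change score: s² + s² − 2rs² = 2(1−r)s².
- ANCOVA: (1−r²)s².
- Ratio of ANCOVA to change score: (1−r²) / [2(1−r)] = (1+r)/2.
- The change score is noisier than the follow-up score alone when 2(1−r) > 1, that is r < 0.5.

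**Power under the planned test.** Take an effect that has 80 % power under ANCOVA, so its expected z value is 1.96 + 0.84 = 2.80. Under the change score this becomes 2.80 × √((1+r)/2), and power is Φ(that − 1.96).

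| r | change (× s²) | ANCOVA (× s²) | ratio | 270 × ratio | power by change score |
|---|---|---|---|---|---|
| 0.3 | 1.40 | 0.91 | 0.65 | 175.5 | 62 % |
| 0.5 | 1.00 | 0.75 | 0.75 | 202.5 | 68 % |
| 0.7 | 0.60 | 0.51 | 0.85 | 229.5 | 73 % |
| 0.9 | 0.20 | 0.19 | 0.95 | 256.5 | 78 % |

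The fifth column is the number of patients who, under ANCOVA, would give the precision that 270 give under the change score.

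**Unequal SDs.** Baseline mRS is cut off at 4, so equal spread cannot be taken for granted. In general, Var(change) = s0² + s1² − 2r·s0·s1 and Var(ANCOVA) = s1²(1−r²). The difference is s0² − 2r·s0·s1 + r²s1² = (s0 − r·s1)², which is never negative. So, apart from the one degree of freedom spent on the covariate, ANCOVA is not less precise whatever the SDs. If baseline is less spread than follow-up, the gain can be smaller than in the table, and the point below which change is worse than the follow-up score moves to r = s0/(2·s1).

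**Limit.** These formulas describe the t-test branch. They do not quantify the Mann-Whitney branch.

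**The case against.** The best defence is that a change score does use the baseline and, in a randomised comparison, is unbiased. The choice is then between two valid analyses of secondary outcomes. The size of the loss rests on a correlation that the article does not give, and at r = 0.9 it is only 5 % of the variance. All of this stands, and it limits the weight of the point. It does not remove it, because the adjusted analysis is no less precise at any r and needs no new data.

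A reader might go further in four ways that the document does not support.

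- **That the comparison is made only among patients still alive, and is therefore biased.** The article does not say this. Its term for enrolled patients is stroke survivors, which is not an analysis set of those alive at a visit, and it states intention to treat. How deaths are scored could be settled in an analysis plan that is not shown.
- **That about 36 of 300 patients would be lost.** This multiplies 300 by the "a 12 % mortality in the first year post discharge" cited in the Background. That figure comes from another hospital-based study and is not a design assumption. This trial takes first-ever, medically stable strokes returning home and excludes serious concurrent illness, so its mortality may be lower. Bias would also require deaths to differ by arm.
- **That the baseline is wasted.** It is used, but inefficiently.
- **That the trial has no precision to spare because it is underpowered.** Whether the sample size supports the stated power concerns the primary end-points and is a separate question. No power is claimed for the functional scales.

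**Conclusion.** The point holds as a matter of efficiency. The article fixes an unadjusted test on change from baseline for three functional scales where a baseline-adjusted analysis is available from the same data. With equal variances, adjustment removes (1−r)/2 of the variance: 35 %, 25 %, 15 % and 5 % at assumed r of 0.3, 0.5, 0.7 and 0.9. Below r = 0.5 the planned change score does worse than ignoring baseline. These sizes depend on r and on the equal-variance assumption, and they apply to the t-test branch only. The direction of the result depends on neither.

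That the article is silent on deaths in these comparisons is a secondary point about clarity, not a demonstrated bias. The primary conclusion is not affected.

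**What to change.** Replace the change-score tests under Secondary end-points with models of the follow-up score that include arm and the baseline value of the same scale:

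- **NIHSS and Barthel Index:** ANCOVA, with a rank-based or ordinal model adjusted for baseline if the scores are skewed.
- **mRS:** ordinal logistic regression adjusted for baseline mRS.

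State also how deaths enter each comparison. In the ordinal mRS model they can be kept as category 6. The outcome is then a composite of death and disability and should be described as such under Secondary study outcomes. For NIHSS and Barthel, do not combine ANCOVA with a worst rank for deaths: a rank is not a score on those scales, so that choice would need a rank-based model throughout.

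The baseline adjustment costs only analysis wording, since the baseline scores are already collected. Counting deaths in the mRS changes an outcome definition and is therefore more than wording. The trial is listed as ongoing, so both changes should be made before unblinded data are seen and sent to the Ethical Review Committee, as the article requires for protocol modifications.

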## Methods

### Study design

This will be a randomized controlled, outcome assessor blinded, parallel group, single center superiority trial in which participants with first ever stroke (both ischemic and hemorrhagic) will be randomized within 48 hours of their stroke to either the video-based education intervention group or the control group [13]. The video-based education intervention group will have health education delivered through short videos which will be shown to the participants and their caregivers at the time of admission, before discharge, and follow-up at first and third month post discharge. The control group will have standard care including pre-discharge education and counseling according to defined protocol. All participants enrolled in this video education intervention group and control group will be followed for 12 months post discharge for assessment of end-points (Refer to Fig. 1).

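### The month-3 satisfaction outcome is to be tested between arms as a change, although controls never receive what is rated and only one assessment is named; separately, caregiver knowledge is defined as a change but analysed as visit means

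*Protocol article*

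**What the plan says.** **Satisfaction and acceptability.** The protocol article, Secondary end-points, names the quantity to be compared as "The change in mean scores for level of satisfaction with the intervention and acceptability of mHealth innovation at the third month follow-up visit". The contrast and timing follow in the same sentence: "at the third month follow-up visit post discharge between the two groups will be calculated", by Student's t test or the Mann-Whitney U test according to the distribution. Under Secondary study outcomes, the instrument is a self-designed tool that "ascertains the constructive and unpleasant attributes of using this mHealth technology". On its administration, that section says: "This self-designed tool will be administered by a research supervisor who will be unblinded to the randomization group".

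On the comparator, Study design states: "The control group will have standard care including pre-discharge education and counseling according to defined protocol". The Standard of care section lists instructions, booklets, a discharge summary and clinic appointments, with no videos. The Intervention section places the memory card with the application in the phones of the intervention group.

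**Caregiver knowledge.** Secondary study outcomes defines this as a change: "a knowledge questionnaire will be administered at 1, 3, 6, 9 and 12 months post discharge and change in score will be ascertained". Secondary end-points analyses something else, the caregivers' "mean score of knowledge regarding stroke risk factors, stroke rehabilitation and medications at each follow-up visit between the two groups".

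**The concern.** A two-sample test needs the same quantity measured in both arms, and a change needs two measurements. The satisfaction analysis as written has neither. If someone carried it out literally, they would have to fill the control arm with answers about something those dyads had not used, or with nothing, and would have to choose a reference value that the plan does not give. A p value from that exercise would have no interpretation, yet it would be reported beside properly randomised secondary comparisons.

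For knowledge the problem is different and smaller. The outcome definition and the analysis name two different quantities. Whoever writes the report could present either as the planned one, and the plan would not settle which.

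**Working it through.** The plan states no figure that this point depends on, so the check is to set out, for each outcome, what is measured, when, in whom, and what is then tested.

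**1. Satisfaction and acceptability**

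- Quantity tested: change in mean score (Secondary end-points).
- Assessment times named: month 3 only. That is 1 time point, and a change needs at least 2.
- Reference for the change: none given. The paragraph just before it ties the changes in NIHSS, Barthel Index and mRS to baseline, so the plan supplies a reference where it means one. For satisfaction with the videos no reference before exposure could exist.
- Content of the tool: good and bad features of using the technology (Secondary study outcomes).
- Exposure by arm: 150 intervention dyads are planned to receive videos and application (Sample size calculation; Intervention). The 150 control dyads receive standard care (Study design; Standard of care).
- Control dyads with the intervention to rate: 0 of 150.
- Later access: Ethical considerations says the videos will eventually be shared with all participants. It does not say by month 3, and the compliance section sets out steps to prevent contamination.

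Either failure alone would stop the test. With no change score, the test has no defined outcome. With no control exposure, it has no second sample.

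**2. Caregiver knowledge**

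| Item | Secondary study outcomes | Secondary end-points |
|---|---|---|
| Quantity | change in score | mean score |
| Times | months 1, 3, 6, 9, 12 | each follow-up visit |
| Reference for change | not stated | not needed |

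- Listed administrations: 5, all after session 1 (enrolment) and session 2 (discharge).
- Baseline interview (Identification and enrollment): described for stroke survivors, covering socio-demographic, clinical and functional items. Caregiver knowledge is not listed.
- Pre-test questions (Measuring adherence to video intervention): these exist, but inside the movie application, so they can serve the intervention arm only.
- Stated pre-intervention scores common to both arms: 0.
- What can be computed: arm means at each of the 5 visits, and changes between follow-up visits. What cannot be computed from the schedule as stated: a between-arm comparison of change from before the intervention.
- Is the planned analysis valid? Yes. Under randomisation, visit means can be compared between arms without a baseline score.

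The knowledge issue is therefore a conflict between definition and analysis. The analysis itself can be carried out.

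**The case against.** The best defence on satisfaction is that acceptability of mobile health in general could be put to controls as a hypothetical question, so some control data might exist. That is possible, and it means the absence of control data is certain only for satisfaction with the videos. It does not rescue the sentence: satisfaction with the intervention is tested in the same breath, the tool is described as rating use, and a single assessment still yields no change. Nor does the brevity of a journal article excuse it, because the analysis is stated and not merely left out.

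On knowledge the defence is stronger. A reader might infer that the plan will test change from month 1 and so subtract whatever was learned from the first two sessions, shrinking a real effect. The documents do not support that. No section names month 1 as a reference, and the only analysis specified compares visit means, including month 1, so early gains are counted. Any figure for lost effect would rest on an assumed share of learning by month 1 and would attach to an analysis that nobody has planned.

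A reader might also infer that knowledge is never measured before the intervention. That goes too far. The application carries pre-tests in the intervention arm, and the data collection forms are additional files not shown here, which could include a baseline knowledge section for both arms. What can be said is that the article states none.

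**Conclusion.** The satisfaction point holds. A stated between-arm analysis cannot be carried out meaningfully: 0 of 150 planned control dyads receive what is rated, and 1 assessment is named where a change needs 2. This rests on controls having no access to the videos by month 3, which the Study design, Standard of care and Intervention sections all imply.

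The knowledge point holds only as a mismatch. One section calls the outcome a change, with no stated baseline common to both arms; the other analyses the score at each visit. The analysis is sound and the definition should follow it. No loss of effect is claimed or quantified.

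Both concern secondary outcomes, and the primary conclusions do not depend on them. They should still be corrected before analysis, since the first would otherwise yield an uninterpretable p value and the second leaves the reported quantity open.

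**What to change.** **Satisfaction and acceptability.** In Secondary end-points, delete the between-group test and the word change. State that month-3 scores will be summarised in the intervention arm only, descriptively and with confidence intervals. Cost: wording. No data collection changes.

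**Knowledge.** In Secondary study outcomes, define the outcome as the caregiver's score at each visit (months 1, 3, 6, 9 and 12), matching the planned analysis. First check the data collection forms. If they hold a baseline knowledge score taken in both arms before the intervention, say so and compare visit scores adjusted for it. Cost: wording and a look at the forms.

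Adding a new pre-randomisation questionnaire now is not the main remedy. The trial is listed as ongoing, so it could not recover a baseline for dyads already enrolled, and the comparison of visit means does not need one.
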